### Description of EPaL intervention

EPaL promoted three main components of healthy lifestyles: (1) healthy eating, (2) positive body image and (3) active lifestyle. The intervention sought to prevent overweight and disordered eating among secondary school adolescents. The rationale of EPaL is that adolescents with positive body image and right response to body signals are more likely to adhere to a healthy lifestyle, eat healthy and stay physically active; and when balance is achieved between energy gained from food and energy lost during physical activity, optimal body weight status ensues.

EPaL adopts the principles of Social Cognitive Theory (SCT) [27], which emphasises the importance of social and environmental factors in determining the psychosocial and behavioural risk factors of both obesity and disordered eating. Hence, EPaL was designed to address socio-environmental factors, such as peer support, presence of a role model, opportunities for practicing healthy eating in/outside the house and opportunities for practice active lifestyle indoors/outdoors; personal factors, such as self-esteem, body image, body weight status/ BMI and self-efficacy of healthy eating and physical activity; and behavioural factors, including self-control/self-regulation, skills to practice healthy eating, physical activity and positive body image, eating behaviour, physical activity behaviour and binge eating behaviour.

EPaL provides students with cognitive and behavioural skills to effect change in targeted behaviours. It aims to alter disordered eating behaviour, promote physical activity, prevent sedentary lifestyle and enhance eating behaviours by encouraging eating in all meal time, consumption of fruits and vegetables and lowering sweetened beverages intake.

According to SCT principles, peers acting as educators should accept increasingly important roles towards developing adolescents’ self-awareness [27]. EPaL intervention are based on the observational learning concepts of SCT and it was designed to engage adolescent educating peers in promoting health by means of cooperation and information sharing. Adolescents tend to accept new information and change their behaviours when observing and learning from their peers [28].

In the present intervention, peer education was used as a strategy to convey health-based knowledge and skills to adolescents. ‘Peer-educators’ referred to students delivering educational material to other students of nearly the same age [29]. For instance, in this study, Form 2 students (14 years old) will deliver the programme to Form 2 and Form 1 students (13 years old). The peer educators will be chosen by the teachers based on academic performance and willingness to convey the intervention message to other students.

All intervention activities will be carried out in a club called ‘EPaL club’, which is established by the research team with the due permission of the school. The purpose of the club is to generate a feeling of belonging among the participants, as well as to allow teachers and the research team to easily monitor the implementation of the intervention.

Prior to the development of EPaL intervention, needs assessments were conducted as follows:Twelve focus groups (*n* = 72) with adolescents aged 13–14 years. The groups engaged in discussions designed to assess the perceptions of adolescents in respect of healthy eating habits, body shape/size and physical activity. The discussions explored strategies that adolescents follow to stay health and the obstacles that prevent adolescents from eating healthy and being active.A nationwide survey was conducted involving 9677 adolescents aged 12–19 years. It aimed to determine the prevalence and factors of underweight, overweight, obesity and disordered eating among Malaysian adolescents.

The EPaL intervention consisted of eight topics which will be delivered by peer educators over the course of 16 weeks, with a two-week gap between every two topics. Each session will take about 60–90 min and the sessions will be held during co-curriculum periods at the school hall in EPaL club. Topics’ titles, key messages and learning outcomes are shown in Table 1.

**Table 1 Tab1:** Objective, key message and learning outcome of EPaL topics

Topics and aims	Key message	Content
Topic 1 *Know Your Body Image and Body Weight Status* • To promote positive body image. • To promote healthy body weight status.	Achieve positive body image and healthy body weight status	• Presentation: - 5 simple steps to determining body weight status: 1. Measure weight. 2. Measure height. 3. Calculate age in years and months. 4. Calculate body mass index using the given formula. 5. Mark the value of BMI and age on the BMI-for-age chart. - Things to do after determining your own body weight status. - Body image discussion. ▪ Effects of negative body image. ▪ Definition and effects of positive body image. • Activities: - Measure height and weight; calculate age and BMI; and determine your own body weight status. - Compare your own body size perception with actual body weight status and learn about your own body image.
Topic 2 *Achieve Healthy Body Weight* • To identify the concept of energy balance. • To describe ways to eat regularly at specified times during the day.	Understand the needs of your own body and achieve energy balance by eating nutritious foods regularly at specified times during the day.	• Presentation: - Energy balance model. ▪ Ways to achieve energy balance in daily life. - Recommend walking for 10000 steps a day. ▪ Advantages of achieving 10000 steps a day. ▪ Type and duration of exercises comparable to walking 10000 steps. - Introduce 5 main meals: breakfast, morning snack, lunch, afternoon snack and dinner. ▪ Recommended time to consume main meals. ▪ Advantages of eating at specified time points. • Activities: - Introduce the pedometer and discuss how to use it. - Perform physical activity and read the number of steps counted by the pedometer. - Participants share when they usually consume the main meals and peer educators share the recommended time points for main meals during the day.
Topic 3 *Follow the Malaysian Food Pyramid* • To eat in a way that conforms to the concept of SPS (S: seimbang/ balance, P: pelbagai/ variety, S: sederhana/ moderation) and the Malaysian Food Pyramid. • To plan daily menus according to the suggested serving size.	Have balance in food, a variety and eat in moderation to stay healthy.	• Presentation: - Malaysian Food Pyramid: food groups in each level and recommended serving size for each food group. • Activities: - Station game with each station referring to a food group. Interactive activities and hands-on skills related to the respective food group in every station. - Menu planning for one day.
Topic 4 *Active according to Physical Activity Pyramid* • To reducing screen-viewing time. • To increase daily physical activity following the Physical Activity Pyramid.	Reduce screen time and increase physical activity to be healthy and brilliant adolescents.	• Presentation: - Physical Activity Pyramid: physical activities of every level and recommended frequencies. - Definition and examples of sedentary activities. - Screen time to be limited to 2 h daily. • Activities: - Match the physical activity with the frequency in the respective level using an empty Physical Activity Pyramid. - Modify a daily activity for a more active lifestyle by cutting screen time and using the extra time to be active. - Groups of participants race to perform physical activities shown in the Physical Activity Pyramid upon stepping on the pyramid levels drawn on the floor. - Wear pedometer during activities and check the steps count after finishing.
Topic 5 *Choose Your Food Wisely* • To choose healthier foods and beverages by comparing product labels. • To order healthier food and beverages when eating out.	Choose healthier foods based on nutrition labels and cooking methods. Healthy food is not only delicious but also good for your health!	• Presentation: - Food labelling. ▪ Information on food labels. ▪ Steps to read a food label. ▪ Steps to read the nutrition information panel. ▪ Ways to compare and purchase foods and beverages based on the information on the labels. - Tips for healthy eating when eating out. • Activities: - Comparing foods and beverages by consulting the product label. Choose healthier products to purchase. - Order healthier foods and beverages from a restaurant’s menu.
Topic 6 *Move Actively Anywhere!* • To increase physical activity by exercising according to the recommendations of the physical activity pyramid. • To do fun exercise.	Be active as much as possible, anywhere!	• Presentation: - Types of exercises to be performed indoors, especially at home or while sitting. - Advantages of a healthy lifestyle. - How to warm up before an exercise and cool down afterwards. • Activities: - Groups of students race to do physical activities fixed for every check point provided. - Aerobic exercise. - Wear pedometer during the activity and check the steps count upon finishing.
Topic 7 *Handle Perceptions Wisely, Accept the Uniqueness of Every Individual* • To identify ways to handle perceptions about one’s own body. • To accept the uniqueness and qualities of you and others.	Practice to achieve positive body image: i) Handle body perceptions wisely ii) Realize the uniqueness of others.	• Presentation: - Ways to handle perceptions and dissatisfaction with your own body. - Ways to prevent comparing between one’s own body and others’. • Activities: - List your physical characteristics and identify what others like about their bodies and qualities they are not satisfied with (if any). - Perform role-play to master ways to respond to statements of dissatisfaction by others. - Identify the qualities of a successful person. - Identify the similarities among your group members, as well their specific strengths and unique qualities. Share your findings with the other group members.
Topic 8 *Happy Practicing EPaL Lifestyle!* • To identify obstacles and solutions in relation to adopting a healthy lifestyle. • To enhance confidence in relation to adopting an EPaL-compliant lifestyle.	Happy practicing of EPaL lifestyle by eating healthy and balanced food, maintain a positive body image and an active lifestyle.	• Presentation: - Ways to gain confidence to maintain an EPaL lifestyle on the long run. • Activities: - Sharing the changes participants made over the course of this intervention. - Sharing the obstacles participants faced when practicing what they learnt in the EPaL programme. - In groups, participants recall one health message taken from EPaL and convey it to others. - Oath taking to adopt an EPaL-compliant lifestyle.

EPaL educational modules Version 1 and 2 focused on equipping peer educators with the necessary knowledge and skills to conduct sessions and educate others, whereas the activity book Version 1 and 2 was intended to serve as a guide for adolescents while performing the programme’s activities.

The Educational Materials for EPaL Version 1 and 2, as well as educational and activity cards and posters were developed and will be used by peer educators during interactive activities. The intervention consisted of two phases:Phase 1: This phase comprised of topics 1–4 with the goal of providing adolescents with the basic knowledge and skills to adopt a healthy lifestyle.Phase 2: This phase covered topics 5–8 with the goal of enabling adolescents to apply the knowledge and skills that they gained in Phase 1.

Peer educators received a Peer-Educator Training kits, which included EPaL modules, an activity book and related educational materials. The participants received an activity book and related educational materials.

A two-phase, 2-day training-of-trainer (TOT) course will be conducted to empower peer educators and provide them with knowledge and hands-on skills relevant to the intervention. TOT sessions were conducted by undergraduate and postgraduate students of nutrition and dietetics. Training for phase 1 will be carried out prior to the implementation of the first topic of the intervention. Training for phase 2 will be carried out after peer educators implemented the intervention activities of phase 1 at the school. The two phases are separated as such so that peer educators could better comprehend the content of the programme and deliver that content to their peers. Feedback from the facilitators will be given immediately after peer educators performed role playing to deliver EPaL topics as part of TOT. They will later asked to conduct eight intervention sessions before a small audience of their peers.

During these sessions at EPaL club, two peer educators will conduct the intervention in small groups of 5–7 participants. As a session begin, attendance will be taken, following which answer on the previous topic worksheet will be discussed. Then, the topic of the present session will be introduced and an ‘interaction session’ followed, in which presentations will be delivered by the peer educators and interactive activities will be demonstrated. Before a session concluded, the participants will be asked to set a goal to achieve on a personal level in tandem with the topic, and answer an exercise sheet designed to assess their understanding of the topic. Peer educators will conclude every session by handing out a feedback form to be filled by the participants to rate their satisfaction with the way the topic was presented. The participants also had to answer two questions in the form related to the topic of the session. The forms will be filled by the participants and collected by the peer educators.

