## Methods/Design

### Study design

EPaL is a school-based intervention programme targeting adolescents in the early years of secondary school. The present study adopted a quasi-experimental design, in which adolescents from one school were included in the intervention group, while those from another school served as the comparison group and were not subjected to the intervention until the end of the period of experimentation. Adolescents in the comparison group attended a standard physical and health education class at least once a week. As the study was concluded, they were allowed to receive EPaL modules and educational materials. A flowchart of the intervention is shown in Fig. 1.

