### Sample size calculation

The sample size calculation was based on the differences between groups (overweight and obese; and non-overweight and non-obese) in the proportion of having disordered eating. The value was taken from the outcome of needs assessment study, which was conducted involving 9677 adolescents aged 12–19 years throughout Malaysia. Based on the study, the proportion of overweight and obese adolescents who were having disordered eating was 40.3 %, whereas the proportion of non-overweight and non-obese adolescents who were having disordered eating was 27.9 %. Assuming a power of 80 % and a level of significance of 5 %, we needed 234 participants for each intervention and comparison groups, respectively. The effect size for proportions was estimated by the differences in the arcsine transformations of the respective proportions. The medium effect size of 25.4 % was obtained.

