### Data analysis

Data will be analysed by using version 21 of the IBM SPSS Statistical software (IBM SPSS Statistics, Inc., Chicago, IL, USA). Depending on the distribution of the variable of interest, descriptive statistics of continuous data will be presented by using the mean and standard deviation, and the median and the inter-quartile range. Categorical data will be presented as frequencies and percentages. *T*-test will be used to detect differences between groups for continuous variables, while chi-square will be used to investigate possible correlations between categorical variables. The repeated measures analysis of variance (ANOVA) will be used to detect significant differences within the groups. The evaluation of the intervention will be based on an intention-to-treat analysis. Differences with *p*-values < 0.05 were considered significant.

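### Peer-led small groups exist in the intervention arm only, yet the planned t-test and chi-square treat all students as independent; if outcomes correlate within groups, that arm's standard errors are too small

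*Protocol article*

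**What the plan says.** The allocation unit is the school, with one per arm: "adolescents from one school were included in the intervention group" and those of a second school form the comparison (Study design). The programme has "eight topics which will be delivered by peer educators over the course of 16 weeks", and at each session "two peer educators will conduct the intervention in small groups of 5–7 participants" (Description of EPaL intervention). The other arm has no such structure: "Adolescents in the comparison group attended a standard physical and health education class at least once a week" (Study design).

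For the analysis, a t-"test will be used to detect differences between groups for continuous variables", and "chi-square will be used to investigate possible correlations between categorical variables" (Data analysis). Repeated measures ANOVA is named for changes within each arm. It deals with repeated occasions on one student, not with students who share a group. No random effect, cluster adjustment or robust standard error is named.

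The sample size of 234 per group comes from two proportions, 40.3 % and 27.9 %: "Assuming a power of 80 % and a level of significance of 5" % (Sample size calculation). That section mentions neither a design effect nor an ICC.

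**The concern.** Students taught together by the same peers share the educators' skill and the norms of their group. The article gives reasons to expect this. It builds the programme on observational learning among peers, describes this age as one at which group norms form, and has teachers choose the educators from among the students, so skill is likely to differ between pairs. If the mechanism works as intended, outcomes within a group will be more alike than outcomes across groups.

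The t-test and chi-square then use too small a variance for the intervention arm. Intervals come out too narrow, p-values too low, and the power attached to 234 per group too high. An unseen analysis plan does not settle the point, because the article itself names the tests, and they do not fit the delivery it describes.

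**Working it through.** **Inputs from the article.** Group size 5–7; 234 students per arm; proportions 40.3 % and 27.9 %; power 80 %; significance 5 %; effect size by arcsine transformation.

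**Assumed, because not given.** Two-sided test; ICC ρ from 0.01 to 0.10; m = 6 per group; groups stable over sessions; comparison students independent; no school effect.

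**1. The plan's own figure.** h = 2·arcsin√0.403 − 2·arcsin√0.279 = 0.2626. Then n = 2·((1.960 + 0.842)/h)² = 227.7, or 228 per group; the pooled two-proportion formula gives 229. The stated 234 is within 3 % of both, so it is in effect an individual-level figure with no material allowance for clustering. (The article reports an effect size of 25.4 %, whereas its proportions give 26.3 %; h = 0.254 would need 244 per group. The steps below use 0.2626.) Power at 234 without clustering is Φ(0.2626·√(234/2) − 1.960) = 81.1 %.

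**2. Clustering in one arm.** With equal arms:

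- design effect in the intervention arm: DE = 1 + (m − 1)·ρ
- variance ratio of the difference: R = (DE + 1)/2
- standard error of the difference multiplied by √R
- type I error of the unadjusted test: 2·Φ(−1.960/√R)
- power: Φ(h·√(234/(DE + 1)) − 1.960)

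For ρ = 0.10: DE = 1 + 5 × 0.10 = 1.50; R = 1.25; √R = 1.118; type I error 2·Φ(−1.753) = 8.0 %; power Φ(2.540 − 1.960) = 71.9 %.

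| ICC | DE | SE, intervention arm | SE of difference | Type I error (no school effect) | Power at 234 per group |
|---|---|---|---|---|---|
| 0.01 | 1.05 | ×1.025 | ×1.012 | 5.3 % | 80.1 % |
| 0.02 | 1.10 | ×1.049 | ×1.025 | 5.6 % | 79.2 % |
| 0.05 | 1.25 | ×1.118 | ×1.061 | 6.5 % | 76.4 % |
| 0.10 | 1.50 | ×1.225 | ×1.118 | 8.0 % | 71.9 % |

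**3. Group size.** At ρ = 0.10, m = 5 gives DE 1.40, type I error 7.4 % and power 73.7 %; m = 7 gives 1.60, 8.6 % and 70.2 %. If the two educators are analysed with a group of seven (m = 9), the figures are 1.80, 9.8 % and 67.0 %.

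**4. Sample size for 80 % power.** (DE + 1)·((1.960 + 0.842)/h)² at m = 6 gives about 234, 257 and 285 per arm at ICC 0.01, 0.05 and 0.10.

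**5. Can the group effect be estimated?** 234/7 = 33.4 and 234/5 = 46.8, so there would be about 33 to 47 small groups in the intervention arm, which is enough for a random effect.

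**6. Comparison with the school layer.** An assumed school ICC of only 0.01 with 234 students per school gives DE = 1 + 233 × 0.01 = 3.33 and type I error 2·Φ(−1.960/√3.33) = 28 %. The small-group layer is the lesser of the two.

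**The case against.** The strongest reply is that the size of the effect is unknown and a larger problem overshadows it. The article gives no ICC, and at 0.01 the effect is trivial: about 1 % on the standard error of the difference. With one school per arm, school and treatment cannot be separated, so a small-group adjustment may give intervals that look corrected while the larger component remains. The article already concedes that randomisation was limited to selecting schools. All of this stands. It makes the point conditional and secondary, but a layer that cannot be repaired is no reason to leave a repairable one.

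Several stronger readings are tempting and are not supported:

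- **That the groups are fixed.** The article does not say that membership or educator pairs stay the same. Opening each session with the previous topic's worksheet hints at continuity but does not establish it. If groups are re-formed, the correlation is probably weaker and spread over several memberships, and the simple design effect no longer describes it.
- **That the promised 80 % power is certainly missed.** At ICC 0.01 it is still 80.1 %. That calculation also contrasts overweight or obese students with the others, not intervention with comparison, so it is not power for the intervention effect in the first place.
- **That the grouping is already in the data.** Attendance is taken at each session, but the article does not say that it is kept by small group.
- **That the t-test assumes equal variances.** The article does not say which form is meant. The unequal-variance form would not help, because it too treats students within an arm as independent.

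**Conclusion.** The point holds conditionally. Delivery is grouped in one arm only, and the named between-arm tests ignore the grouping. With a positive within-group correlation, the intervention-arm standard error is understated by a factor of 1.02 to 1.22 and that of the difference by 1.01 to 1.12, for ICC 0.01 to 0.10 and 6 per group. The effect is negligible at the low end and worth correcting from about 0.05 upwards.

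A reader might take 5.3 to 8.0 % as the trial's actual type I error. It is not: it is the contribution of this layer with the school effect set to zero. The figures also rest on an assumed ICC, stable groups, and comparison students treated as independent although they too attend classes. A pair of educators leading more than one group would make the effective cluster larger; the article does not say whether that happens.

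**What to change.** - **Record** each intervention student's small group, any change of group, and which group or groups each peer educator leads. State whether the educators are analysed and, if so, place them with the group they lead; the Discussion expects benefit in them too.
- **Replace** the t-test and chi-square for the intervention comparison with a partially nested mixed model: linear for continuous and logistic for binary outcomes, with a random effect for small group in the intervention arm only. For binary outcomes, report a marginal contrast, because a random effect in one arm makes the raw logistic coefficient hard to interpret. Small-sample-corrected cluster-robust standard errors by small group are an acceptable alternative. If groups are re-formed between sessions, say how membership will be assigned or weighted.
- **Report** the estimated ICC.
- **State plainly** that this does not remove the confounding of school with treatment, so p-values and intervals remain conditional on no school effect.

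The cost is one more identifier to record, a different model statement, and intervals wider by about 1 to 12 % over the assumed ICC range.
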